### Mediating variables

*Adherence to medication* is assessed through patient and family reports (when available), and pill counts are conducted by the evaluator. Ratings are made on a five point scale ranging from 0 = not taking medication when prescribed, to 5 = taking medication all of the time as prescribed.*Working alliance* with respective service providers is measured with the Working Alliance Inventory-patient version, a self-report instrument [52]*Premorbid adjustment* has been shown to be of importance to clinical outcome [11,18] and is assessed with the Premorbid Adjustment Scale [60] at time of entry into the trial in case that such data was not already collected as part of the initial protocol of entry into PEPP-Montreal.

### Economic analysis

Administrative databases are utilized to assess costs associated medical services. The Regie de l’Assurance-maladie du Quebec (RAMQ) provides free public health and prescription drug insurance plans to all eligible Quebec residents. RAMQ databases are consulted for physician services (all patients) and filled prescriptions for patients with public coverage (approximately 90% of patients), and Med-Echo, for hospitalizations. Questionnaires, administered at baseline and every three months following are utilized to record data on any other health care usage as well as for patient and family time involvement in receiving such treatment. We request consent to access this database as part of the initial informed consent. This information is used to track overall societal and economic costs associated with patient treatment in both the experimental and control groups.

### Training and inter-rater reliability

All service care providers and assessors acquire intensive onsite training in their field and are supervised by the principal investigator ([name]), co-PI ([name]) and the PEPP research coordinator ([name]). Assessors have achieved high inter rater reliability (range 0.75-0.92) and are able to consult with the project coordinator should any questions arise.

### Power and sample size

Power Analysis for sample size calculation is based on the proportion of SEI patients that were in remission of positive symptoms in the last two years of the OPUS trial (41.8%) [31] and the proportion of SEI patients that were in remission in the last two years of the uncontrolled outcome study conducted at PEPP–London (69%) [32]. Assuming conservatively a 5% greater proportion of patients in remission for the control condition than in the OPUS trial and a 5% smaller proportion for the experimental condition than in the PEPP-London study, it is estimated that a sample size of 82 in each group (total of 164) will achieve 80% power to detect a difference between groups. Given the rates of attrition between the beginning of the third and the end of the fifth years from the OPUS extension trial that were 18% [31] and from the PEPP-London study that were 12% [32], we expect rates of 25% and <20% over the same period from the control and experimental conditions respectively. Recruitment of participants are adjusted from n =164 to n = 212 to account for possible dropouts.

### Participant withdrawal

For the purpose of this trial, dropouts are considered those with three assessments in a row that are missing. To reduce attrition, our study coordinator contacts anyone who has missed two assessments in a row, prior to their next scheduled evaluation. When a dropout has occurred, an effort is made to ascertain the reason for the dropout and to conduct a final assessment for the primary outcome (remission status). If a patient drops out of treatment but continues to consent to using their data, medical files for their case are located to obtain information on many of the outcome measures.

### Statistical analyses

Data analysis is based on the intent to treat principle. All patient evaluations will be included in the analysis. To assess homogeneity at baseline, relevant demographic data will be presented.

For the primary outcome measures, the proportion of patients in remission in the experimental and control groups will be compared using a Pearson chi-square statistic and the mean length of remission with a t-test or Wilcoxon test for independent samples, based on the distribution of the independent variable. Logistic regression analyses and multiple regression analyses will also be performed with all covariates and mediators.

For the secondary outcome measures including relapse (relapse vs. no relapse), dichotomous outcomes will be analyzed using logistic regression with covariates. Time to Event (relapse) will be measured using a Kaplan-Meier methods and Cox regression to analyze intervals of time from randomization to relapse. Continuous outcomes that include clinical outcomes will be assessed using regression models with covariates and finally longitudinal data with repeated measurements will be analyzed using repeated measures of analysis of variance.

Missing data will be assessed to determine if they are random or informative. Should missing data be non ignorable, then selection models and pattern-mixture models will be used to evaluate the robustness of the primary analyses.

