### Inclusion criteria

Our aim is to use inclusion criteria that are as non discriminatory as possible in order to ensure the ecological validity of this trial and to reflect the kinds of diverse patients seen in FEP clinical settings. Although the SEI services treat patients between 14 and 35 years old, for the purpose of the study, patients aged 18–35, with a DSM-IV diagnosis of a psychotic disorder (schizophrenia spectrum psychoses and affective psychosis), who have completed two years of SEI treatment and follow-up within the McGill network of SEI services, an IQ greater than 70, the ability to communicate in either French or English, and the ability to provide informed consent, are eligible for participation. Patients are recruited regardless of their remission status at the end of two years of SEI treatment, consistent with what may be seen in regular clinical practice. Ethics approval for this RCT was granted by McGill University’s Faculty of Medicine Institutional Review Board (Assurance number: FWA 00004545) and from the Douglas Hospital Research Ethics Board.

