### Randomization

Randomization is stratified according to sex and substance abuse to ensure that these two factors, know to influence outcome, are balanced between groups. Once participants have signed informed consent to be randomized, their initials and ID # are given to an on site statistician who is not connected with the service. Randomization to one of the two treatment conditions is conducted using a computerized urn randomization protocol [33]. Post-randomization, patients are asked which condition they would have preferred to be randomized to and if they are satisfied with the allocation they were assigned. Results of the randomization are communicated to the treatment team such that appropriate transfer decisions may be made, in the case that a patient is randomized to regular care. This data will be used as a covariate in case that treatment preference biases outcomes (Figure 1).

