## Discussion

This study is based on previous data that suggests that the benefits of SEI services in FEP at two years are lost at five-year follow up if patients return to regular care [31]. Given the severity of psychosis and the individual and societal costs associated with this disorder, there is a need for research that can better guide best practices. That FEP patients are young and potentially still malleable to treatment, suggests the importance of positively influencing long-term trajectories of outcome. To our knowledge, this is the first RCT trial of its kind in North America, and one of only two such trials anywhere (OPUS-II) [61], being carried out currently to assess the impact of extended SEI for a total of five years in FEP. Several strengths of this study include the number of participants recruited as well as the computerized randomization procedure that ensures chance allocation to group. That we have included FEP patients with comorbid disorders, including comorbid substance use, and that patients in our control condition are likely to be filtered through a wide range of 1st, 2nd, and 3rd line services available, gives critical construct validity to our study. Given that the majority of service is provided out of a single site (PEPP-Montreal) with two satellite clinics that are closely aligned and that follow the same treatment system, homogeneity of service infrastructure and fidelity to the same SEI model of care is ensured. As well, we are measuring a host of critical variables that may give meaning to the context of remission. Variables including social and occupational functioning and negative symptoms at baseline have been shown to impact long-term trajectories in FEP [12,13]. Measures of quality of life bring into focus the personal perspectives of this disorder while concurrent measures of all associated economic costs will highlight societal burden. This trial is registered http://www.isrctn.com/ (ISRCTN11889976), which helps to ensure complete reporting.

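### The primary tests are valid but leave out sex, substance abuse and remission status at entry, and so forgo a modest amount of power and precision

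*Protocol article*

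**What the plan says.** The Statistical analyses section of the protocol article names the primary comparisons. For the proportion, "the proportion of patients in remission in the experimental and control groups will be compared using a Pearson chi-square statistic". For duration, the plan is to compare "the mean length of remission with a t-test or Wilcoxon test for independent samples". Neither has a covariate. The same paragraph adds: "Logistic regression analyses and multiple regression analyses will also be performed with all covariates and mediators". Relapse and the other secondary outcomes are given regression models with covariates.

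Three other places bear on this:

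- Randomization: "Randomization is stratified according to sex and substance abuse to ensure that these two factors, know to influence outcome, are balanced between groups". Allocation is by urn: "Randomization to one of the two treatment conditions is conducted using a computerized urn randomization protocol".
- Inclusion criteria: "Patients are recruited regardless of their remission status at the end of two years of SEI treatment".
- Discussion: "Variables including social and occupational functioning and negative symptoms at baseline have been shown to impact long-term trajectories in FEP".

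The Mediating variables section lists medication adherence and working alliance, which are followed through the trial, alongside premorbid adjustment, which is a baseline variable.

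**The concern.** The design uses sex and substance abuse because they are prognostic, and the primary test then discards them. Remission status at entry is neither a stratification factor nor a covariate. The endpoint is remission itself, and low negative symptoms are part of its definition, so entry status is a natural candidate for a strong predictor.

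The regression sentence does not fill the gap. It describes additional analyses, and it puts mediators beside covariates. The Background hypothesises that adherence mediates the difference in remission; a model that conditions on adherence removes part of the effect the trial is meant to measure. As written, no analysis of the primary outcome adjusts for baseline variables only.

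At stake are some power, some precision on the risk-difference scale, and protection of the primary estimate against chance imbalance in entry remission.

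**Working it through.** **1. Reproduce the planned sample size.** Inputs from Power and sample size: 41.8% (OPUS) raised by 5%, 69% (PEPP-London) lowered by 5%, 80% power. Alpha is not stated; two-sided 0.05 is assumed.

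Read as relative shifts: 0.418 × 1.05 = 0.4389 and 0.69 × 0.95 = 0.6555; difference 0.2166, mean 0.5472.

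n = [1.960 × √(2 × 0.5472 × 0.4528) + 0.842 × √(0.4389 × 0.5611 + 0.6555 × 0.3445)]² / 0.2166² = (1.380 + 0.578)² / 0.0469 = 81.7, so 82 per group, with power 80.1%.

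Average dropout of 22.5% (25% and 20%): 164 / 0.775 = 211.6, so 212. Both stated figures reproduce, and they are figures for the unadjusted test.

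Read as percentage points (46.8% against 64%), the same formula gives 130 per group, and 82 per group has about 60% power. That is a separate matter.

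**2. Power with and without adjustment.** Simulation with 2,500 trials per row (Monte Carlo error about 0.5 to 1 point), stratified allocation, 43.89% against 65.55%, and 50% in remission at entry. The article gives no prognostic strengths, so all odds ratios and the entry proportion are assumed.

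| Per arm | OR of each stratum factor | OR of entry remission | Chi-square | + sex, substance abuse | + entry remission |
|---|---|---|---|---|---|
| 82 | 1.5 | 1 | 82.2% | 82.2% | 82.5% |
| 82 | 1.5 | 4 | 79.8% | 80.2% | 84.1% |
| 82 | 1.5 | 8 | 80.3% | 80.5% | 87.8% |
| 82 | 2.5 | 4 | 80.2% | 82.8% | 86.3% |
| 82 | 2.5 | 8 | 80.0% | 81.2% | 89.2% |
| 110 | 1.5 | 4 | 90.8% | 91.1% | 94.6% |
| 110 | 2.5 | 8 | 90.0% | 91.1% | 96.5% |

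Over all scenarios run on these rates, the strata alone gain 0 to 2.6 points at 82 per arm. The full model gains 0.3 to 9.2 points at 82 and 0.2 to 6.5 points at 110.

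With urn allocation, strata ORs of 2 and an entry OR of 3 to 9, the chi-square gives 80–82% and the full model 84–90% at 164 patients. At 220 patients the figures are 89–91% and 93–97%.

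On the percentage-point rates at 110 per arm, the chi-square gives 72–75% and the full model 73–84%.

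**3. Type I error.** With tightly balanced strata and ORs of 2.5 each (6,000 trials, 110 per arm), the chi-square rejects in about 3.9% of null trials, against 4.9% for the strata-adjusted model. With urn allocation and ORs of 2, the chi-square rate is about 4.5–5.8%.

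**4. Chance imbalance.** With 109 and 111 patients and 50% in remission at entry, the SD of the arm difference is √[0.25 × (1/109 + 1/111)] = 6.7 points. A gap of 10 points or more then has probability of about 14% (about 11% if 30% enter in remission). For an entry OR of 3 to 9, such a gap moves the unadjusted risk difference by about 2.6 to 5.0 points. The planned difference is 17.2 or 21.7 points, depending on the reading of the 5%.

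**5. Length of remission.** In a linear model with covariates explaining a share R² of the variance, power is Φ(2.80/√(1 − R²) − 1.96). An 80% power becomes 84%, 88% and 92% for R² of 0.1, 0.2 and 0.3 (assumed values).

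**The case against.** The unadjusted tests are valid under randomisation, and the sample size was computed for them. A reader might infer that this choice leaves the trial underpowered. The documents do not support that: on the reading that reproduces 82 per group, the chi-square has its planned 80%, and about 90% if all 220 randomised patients are analysed. Figures in the low seventies arise only from the percentage-point reading of the 5% shifts, which is a different question.

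A reader might also infer that ignoring the strata makes the test markedly conservative. Urn allocation balances less tightly than blocks, and under it the error rate stays close to 5%. Nor does a chance imbalance at entry invalidate the result, because the test's error rate already allows for it.

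The prognostic weight of entry remission is not given anywhere. The Discussion says only that baseline functioning and negative symptoms affect later course. The part of the gain that rests on the article's own statement about the strata is small.

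Which covariates enter the regression, and whether mediators have a separate model, may be settled in an analysis plan that is not shown. That is fair. But the article does name its primary test, and calls the regression additional.

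Finally, it is tempting to say that every variable needed is already in hand. That is not established. Complete remission requires six months, the study baseline falls within 3–6 weeks after randomisation, and the article does not show that all three sites rated SAPS and SANS before randomisation. This objection stands and shapes the fix.

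**Conclusion.** The point holds as one of efficiency, not validity. The primary comparisons discard two factors the article itself calls prognostic, and an entry status that varies by design; the supplementary regression, with mediators included, cannot take their place.

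The direction is firm; the size is conditional. The two strata are worth roughly 0 to 3 power points. With entry remission added, the total gain is about 2 to 10 points on the rates that reproduce the plan, if the entry odds ratio is 3 to 9, and close to the strata-only gain if entry status predicts little. For the binary outcome, the precision gain is to be read on the risk-difference scale: adjustment in a logistic model raises power but does not shrink the standard error of the log odds ratio.

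The change should be made, but the planned analysis would not be wrong without it.

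**What to change.** Make the primary test of the proportion a logistic regression on arm, sex, substance abuse and entry remission status (or entry SAPS/SANS scores), with no mediators. Report a standardised risk difference with a 95% CI. For length of remission, use a linear model with the same covariates, or a stratified rank test. Keep the chi-square and the t-test or Wilcoxon as sensitivity analyses, and move models containing adherence and working alliance to a separate mediation analysis.

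Fix the source of entry status before any comparison by arm: a pre-randomisation rating where one exists; otherwise the study baseline, stating that it is taken up to 3–6 weeks after randomisation; or else adjust for the two strata only.

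The cost is mainly wording, since sex and substance abuse are known from randomisation. There are two downsides. The odds ratio becomes conditional, which the standardised risk difference answers. And the entry covariate may be missing, or measured after randomisation, for some patients, so its handling must be stated.

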The **primary hypothesis** guiding this RCT is that individuals in the experimental group (extended SEI) will show higher rates and longer periods of remission (both positive and negative symptoms) than the control group over the extension period of three years. The *secondary hypotheses* are that: a) the difference in remission rates are mediated by the level of medication adherence in the two groups; b) as the experimental group is expected to have higher levels of working alliance with their treatment providers than the control group, we hypothesize that the difference in the level of medication adherence between the two groups and retention in treatment is predicted by working alliance; c) that the experimental group will have better clinical outcomes (lower relapse rates and levels of symptoms), functional outcomes (social/occupational functioning), and quality of life than the control group. The economic consequences of extending SEI past the standard current 2 years is also being investigated, within the RCT design, taking into consideration both direct and indirect costs.

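### The supplementary primary-outcome regressions condition on mediators, and conditionally on data asked after allocation, so their arm coefficient is not the intention-to-treat effect

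*Protocol article*

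**What the plan says.** All places are in the protocol article.

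- **Primary comparison (Statistical analyses).** The analysis follows intention to treat. For the first primary measure, "the proportion of patients in remission in the experimental and control groups will be compared using a Pearson chi-square statistic". The second, duration, is tested separately by a two-sample t-test or its rank-based counterpart, depending on the distribution. Both comparisons are unadjusted.
- **Added regressions (same paragraph).** "Logistic regression analyses and multiple regression analyses will also be performed with all covariates and mediators". No regression for the primary outcome is named that leaves the mediators out.
- **Which variables are mediators (Mediating variables, Table 1).** Three are listed: adherence, working alliance and premorbid adjustment. Adherence "is assessed through patient and family reports (when available), and pill counts are conducted by the evaluator", every three months. Working alliance is rated every six months.
- **What the protocol expects of them (Background, hypotheses).** Secondary hypothesis a) is that "the difference in remission rates are mediated by the level of medication adherence in the two groups". Hypothesis b) starts from the expectation that "the experimental group is expected to have higher levels of working alliance with their treatment providers than the control group".
- **Preference data (Randomization).** "Post-randomization, patients are asked which condition they would have preferred to be randomized to and if they are satisfied with the allocation they were assigned". After an intervening sentence on telling the treatment team the allocation, the section continues: "This data will be used as a covariate in case that treatment preference biases outcomes".

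**The concern.** A regression that adjusts for baseline prognostic factors and one that contains a mediator answer different questions. The first estimates the effect of allocation. The second estimates the part of that effect not carried by the mediator, and does so without bias only if nothing unmeasured drives both mediator and outcome. The protocol names one set of regressions for both purposes and places it under the primary outcome without a label.

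The risk lies in interpretation. A reader who sees a crude test beside an adjusted odds ratio will take the second as a refinement of the first. Here the adjusted figure would shrink further the more the intervention works through adherence and alliance, as the protocol theorises. A true benefit could then be reported as weakened or lost after adjustment.

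Data collected after allocation raise a related problem. A preference stated once the arm is known can move towards or away from what was received. Satisfaction with the assigned arm has no value before there is an assignment, so it is a consequence of allocation.

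**Working it through.** **Step 1. Sort the candidate variables by whether allocation can change them.**

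- Sex and substance abuse (stratification factors): fixed before randomisation, safe to adjust for.
- Premorbid adjustment: describes the time before illness. It is safe to adjust for, although listed among the mediators.
- Adherence and working alliance: measured through follow-up. Alliance is expected to differ by arm, and adherence is hypothesised to carry the remission difference. Not suitable for an effect model.
- Stated preference: asked after allocation and open to its influence.
- Satisfaction with the assigned arm: a result of allocation.

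**Step 2. Reproduce the plan's own figure, to anchor the illustration.** The Power and sample size section gives source rates of 41.8% and 69%, each moved by 5%. Read as relative changes:

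- control: 0.418 × 1.05 = 0.4389
- experimental: 0.69 × 0.95 = 0.6555

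The two-proportion formula uses pooled variance under the null, no continuity correction, and two-sided alpha 0.05 (assumed, as alpha is not stated). With a mean rate of 0.5472 and a difference of 0.2166:

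n = [1.96 × √(2 × 0.5472 × 0.4528) + 0.8416 × √(0.4389 × 0.5611 + 0.6555 × 0.3445)]² / 0.2166² = (1.380 + 0.578)² / 0.0469 ≈ 81.7, so 82 per group.

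Dropout: 82/0.75 + 82/0.80 = 211.8, so 212. Both stated figures reproduce, on an unadjusted comparison. The crude odds ratio is (0.6555/0.3445) / (0.4389/0.5611) = 2.43.

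**Step 3. First approximation.** If a share f of the log odds ratio runs through the mediator and there is no confounding, the adjusted odds ratio is roughly 2.43^(1−f): 1.56 at f = 0.50, 1.25 at f = 0.75 and 1 at f = 1.

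**Step 4. Simulation.** One continuous mediator is shifted by treatment by 0.8 of its residual SD. The outcome is logistic and calibrated to the Step 2 rates. Power comes from 400 replicates with 82 per arm. In the confounded case, one unmeasured variable enters the mediator and the log-odds of remission, each with coefficient 0.7. All these settings are assumptions.

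| Share mediated | Crude OR | Adjusted OR, no confounding (power of arm test) | Adjusted OR, confounding (power of arm test) |
|---|---|---|---|
| 0% | about 2.4 | 2.41 (0.74) | 1.97 (0.51) |
| 50% | about 2.4 | 1.61 (0.30) | 1.38 (0.12) |
| 75% | about 2.4 | 1.29 (0.10) | 1.14 (0.07) |
| 100% | about 2.4 | 0.97 (0.04) | 0.77 (0.08) |

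Power without the mediator is about 0.80 throughout.

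**Step 5. Vary the assumptions.**

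- *5% read as absolute points* (46.8% against 64.0%, crude OR about 2.0). The adjusted ORs at 0, 50, 75 and 100% mediated are 2.00, 1.44, 1.20 and 0.98 without confounding, and 1.63, 1.19, 1.01 and 0.77 with it. This reading does not reproduce 82 per group (it gives 130) and serves only as a range check.
- *A different model*: conditional total effect ln 2.43, mediator effect 0.8 log-odds per unit, and an unmeasured cause with coefficient 0.6 on the mediator and 0.8 on the outcome, with mediator noise SD 0.8. Against a marginal OR of about 1.9, the adjusted ORs are about 1.63, 1.20 and 0.85 at 25, 50 and 75% mediated. With the confounder's effect on the outcome removed they are about 1.94, 1.56 and 1.25, against a marginal OR of about 2.2.

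Attenuation appears in every setting with mediation. In these runs a value clearly below 1 appears only with confounding added to a large mediated share.

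**The case against.** The strongest reply is that nothing confirmatory is touched. The chi-square and the t-test or Wilcoxon test come first, the regressions are additional, and the sample size rests on the unadjusted comparison. This stands. A reader might infer that the trial's main treatment estimate is biased or its effect removed; the text does not support that, since nowhere does the arm coefficient of these regressions replace the primary tests.

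Second, a model containing adherence is a legitimate step towards hypothesis a), and the sentence may be the mediation analysis in condensed form. This stands in part. The purpose is legitimate, but the sentence mixes it with covariate adjustment and names no adjusted model without mediators. It also cannot serve hypothesis b) as it stands, because there adherence and retention are the outcomes, not remission.

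Third, a reader might infer that the adjusted effect must be null or reversed if the hypotheses are true. It need not be. Hypothesis a) does not claim full mediation, and a clear reversal needs confounding that the protocol neither states nor quantifies.

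Fourth, the preference covariate is conditional, its stated reason names preference only, and what the covariate sentence refers back to is unclear. It is therefore an inference, not a stated plan, that satisfaction will be adjusted for. Preference may also reflect a settled prior view. What remains is that the answer is collected after the arm is known.

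Finally, the choice of mediation estimator, mediator timing and sensitivity analysis for confounding are commonly left to an analysis plan. Their absence from an article is no finding and is not claimed as one.

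**Conclusion.** The concern holds for the supplementary regressions only. As written, their arm coefficient conditions on adherence and working alliance, which the protocol treats as consequences of allocation, so it does not estimate the total effect that intention to treat requires. It will usually be attenuated: from about 2.4 to between 1.4 and 1.6 when half the effect is mediated, and to between 1.1 and 1.3 at three quarters, under the main simulation. It could reach or cross 1 if mediation is large and mediator and outcome share unmeasured causes. These sizes are illustrations, because the mediated share, the mediator shift and the confounding are all assumed.

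The preference covariate is a smaller version of the same fault. Adjusting for post-allocation preference is questionable. Adjusting for satisfaction, if it is meant, would condition directly on a consequence of the arm. Premorbid adjustment is harmless.

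Severity: should-fix. The text fixes a specification that is wrong for an adjusted effect estimate, but the primary tests and sample size stand.

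**What to change.** Split the regression sentence in Statistical analyses and amend the covariate sentence in Randomization.

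1. **Adjusted effect models for both primary measures:** arm, the stratification factors (sex and substance abuse) and other pre-randomisation covariates. Premorbid adjustment may stay. Adherence, working alliance, satisfaction and post-allocation preference are excluded. Because the baseline visit takes place three to six weeks after randomisation, the covariate list should rest on values that date from before it.
2. **Models containing adherence or working alliance:** label these as mediation analyses for secondary hypotheses a) and b), and do not report their arm coefficient as an adjusted treatment effect.
3. **Preference and satisfaction:** report satisfaction by arm as description only. Use post-allocation preference only in an analysis labelled exploratory or sensitivity. All participants are already randomised, so preference can no longer be collected before allocation.

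The cost is wording and a few more model fits. No new data are needed, and the Trial status section shows follow-up still under way, so the change can precede the final analysis.
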